### **Summary**

Depression is one of the more severe and serious health problems because of its morbidity, disabling effects and for its societal and economic burden. Despite the variety of existing pharmacological and psychological treatments most of the cases evolve with only partial remission, relapse and recurrence.

Cognitive models made a significant contribution in the understanding of unipolar depression and its psychological treatment. Even though, success is only partial and many authors affirm the need to improve those models and also the treatment programs derived from them. One of the issues that requires further elaboration is the difficulty these patients experience in responding to treatment and maintain therapeutic gains across time without relapse or recurrence.

Our research group has been working in the notion of cognitive conflict viewed as personal dilemma according to personal construct theory. We use a novel method for identifying those conflicts using the repertory grid technique. Preliminary results of the current project with depressive patients show that more than 90% of them have one or more of those conflicts. This fact might explain the blockage and the difficult progress of these patients, especially the more severe and/or chronic. These results justify the need for specific interventions focused in the resolution of these internal conflicts.

This project, a logical continuation of the one in execution, aims to empirically test the hypothesis that an intervention focused on the dilemma(s) specifically detected for each patient will contribute to enhance the efficacy of cognitive-behavioral therapy for depression. A therapy manual will be developed and tested using a randomized clinical trial by comparing the outcome of two treatment conditions: a cognitive-behavioral treatment package and another package combining cognitive-behavioral and dilemma-focused interventions. We expect that this combined package will increase the efficacy of one of the more prestigious therapies for depression, a significant contribution for its treatment.

## Background

Depression is an often chronic and recurring health problem, with relapse rates ranging between 50 to 80% and approximately 120 million people currently affected worldwide. An increase in this figure is expected [1] and its lifetime prevalence can be up to 15% [2], this constituting the leading cause of years lived with disability. In 2001, depression was the fourth main cause of morbidity and estimates indicate that by 2020 it could rise to second place, following cardiovascular diseases [3, 4]. Nowadays, depression is considered to present a predominantly chronic evolution with recurring episodes, and it attains such levels of severity that seriously compromises one's quality of life. Furthermore, depression's comorbidity with other mental health problems [5] and with other chronic diseases is very high, and worsens the chance of recovery [2], which further emphasizes the need to advance in the understanding and treatment of depression.

It is estimated that in Spain only 35.8% of patients diagnosed with major depression receive the minimum adequate treatment [6], but even amongst these, complete remission of symptoms is rare. In addition to drug treatments, a variety of existing psychological treatments have proved at least as effective for unipolar depression, without any single one of them standing out as more efficacious. However, cognitive behavioral therapy (CBT) has acquired more prestige and is backed by more research in efficacy [7, 8], without this resulting in a fully satisfactory solution for the treatment of depression. Another issue raised by Haby, Donnelly, Corry and Vos [9] is that the said efficacy cannot be asserted on the basis of existing research in languages other than English. Certainly, efficacy studies in Spanish are scarce and have very small samples.

Some of these problems in treating depression may be due to the fact that "that which we call 'depression' covers different problems and processes" [10]. Perhaps, despite the enormous amount of research and literature on the cognitive factors involved in depression [11, 12], we need new conceptual advances ready to be tested in order to enrich cognitive models of depression. In particular, contributions that allow a better explanation of the difficulties (resistance, relapse, recurrence) encountered in the process of change are needed, difficulties which are also common in other mental disorders or health problems. Thus, these contributions might also be useful for the understanding and treatment of a variety of clinical conditions in which change is difficult to achieve.

Since its inception [13], cognitive therapy for depression was based on the identification of a systematic and persistent negativity in the cognitive processes of depressed patients. Thus, the identification of the negative thoughts which invade the patient's consciousness in an automatic fashion is central to this therapeutic approach. Dysfunctional schemas, attribution bias, rumination and perfectionism are also part of the cognitive model for depression, amongst other factors [14]. But as Beck himself [15, 16] recently pointed out, the formulated model is incomplete and needs to be supplemented.

One aspect which has not been studied and could contribute to explaining the difficulties of these patients achieving change concerns the cognitive processes related to identity conflicts. Our research group has been working for years with a methodology capable of assessing these conflicts and performing empirical studies to evaluate its clinical importance.

### The notion of cognitive conflict

Starting with psychoanalysis, a variety of theories have suggested the existence of internal conflicts which drive people to grueling internal struggles blocking their development, and

creating suffering and symptoms. Heider and Festinger's now classic formulations stand out, which postulated a motivational tendency to resolve these conflicts, and how, when this is not attained, internal conflicts generate a state of psychological tension. Piaget himself [17] proposed the term "cognitive conflict", which in a developmental context serves the function of reorganizing the intellectual processes of children. Unfortunately, and despite the enormous relevance of this notion, it has received little attention in recent decades, largely due to the lack of methods providing operational and measurable definitions.

Personal Construct Theory (PCT) provides an ideal conceptual and methodological framework for the study of cognitive conflicts. Far from being anchored in the rich initial formulations of its creator [18], PCT has undergone considerable development (see, for example, Fransella's extensive compilation [19] or Walker & Winter's review [20]). PCT emerges from a proactive view of human beings as active agents (as later did Bandura [21]) who regulate their motivational and emotional processes as well as their actions, based on the congruence or discrepancy between their construction of "self" and "ideal self" (as suggested also by other authors [22-25]). Thus, it is understandable for the person is to encounter dilemmas or conflicts when having to reconcile his self with his personal values in a decision-making process (although the person might not be consciously aware of those conflicts).

Rowe [26] describes the case of a chronically depressed patient who faced the choice between staying depressed (linked in her system to being "humane"), or improving her mood but becoming a "destructive" or "unpleasant" person (according to her own view). In PCT, the notion of implicative dilemma emerged to designate those conflicts in which the desired change (e.g., stop being depressed) implies, in the context of the network of constructs forming a personal meaning system, undesired changes in one's vision of oneself (e.g., becoming "unpleasant"). When these conflicts occur in the construct system of an individual, his or her capacity for change becomes blocked, which would be relevant to explain both the onset of clinical symptoms as well as the resistance to treatment. Although these cognitive conflicts can coexist with interpersonal conflicts and with secondary gains as postulated by other theoretical approaches, they are independent from these and represent an innovative contribution of PCT.

The Repertory Grid Technique (RGT) [27, 28] stems from PCT as an instrument which allows to assess the self-concept and its cognitive structure. The main advantage of this technique is that it is based on the evaluation made by the person of her or himself and others through her or his own constructs or mental contents, including what she or he considers her or his "ideal self" (see methods section for more details). It is therefore a subjective assessment technique [29], with high levels of utilization (see [30]), which is ideal to capture conflicts in personal meaning systems. The RGT has already been applied in the study of unipolar depression (e.g., [31-33]; see Winter [34] for a review).

One of our group's contributions is the development of a way to evaluate conflicts in relationships between constructs, operationalizing the notion of implicative dilemma (ID) through the RGT [35, 36]. In the first step of our procedure, discrepant constructs are identified when scores between the "self" and "ideal self" differ. In the second, congruent constructs (in which there is similarity between "self" and "ideal self") are also identified. Next, correlations between both groups of constructs are analyzed in pairs, and implicative dilemmas are detected in those cases where the desirable pole of the discrepant construct (e.g., "does not get depressed easily") correlates with the undesired pole of the congruent construct (e.g., "selfish"). In the construct system of the person depicted in this example, overcoming depression in a consistent way would also imply becoming selfish. Also, to make sure she is really "concerned about others" she must remain

depressed. So she is immersed in a dilemma because of the implication that the discrepant construct has for the congruent construct (and vice versa).

Cognitive conflicts might be reflected in the RGT also by the use of dilemmatic constructs, those in which the “ideal self” is rated at midpoint. This might indicate that both poles of the construct designate undesirable characteristics for the self, the person, thus, trying to regulate his or her position in the construct by avoiding the extremes.

### **Cognitive conflicts, depression and psychotherapy**

Preliminary studies with this definition of cognitive conflicts understood as dilemmas have shown their clinical interest. Feixas, Saúl, and Ávila-Espada [37] found that just over half of a group of patients who consulted for psychotherapy (n = 284) presented with IDs, while only a third of the control group did (n = 322). This statistically significant difference was not found with two other procedures used to identify conflicts in the RGT. In addition, participants with IDs had a higher level of symptom severity. Feixas, Montesano, Erazo-Cacedo, Compañ and Pucurull [38], in a pilot study, found a higher proportion (59.60%) of depressed patients with at least one ID (vs. 40.40% of the control group). Also in this study, symptom levels were associated with the number of these dilemmas. In a presentation of preliminary results of an ongoing project with a 81 depressive patients and improved reliability of the RGT application, Feixas, Compañ, Montesano & Saúl [39] found that although cognitive conflicts (including both IDs and dilemmatic constructs) were not specific to depression, they occurred in about 9 out of every 10 patients.

Regarding the effects of psychotherapy on IDs, Feixas, Saúl, Winter and Watson [40] followed a group of 87 patients and found that those who presented these conflicts to begin with tended to resolve them by the end of psychotherapy (although psychotherapy had a variety of orientations and didn't focus on dilemma resolution). Moreover, in cases where this did not happen, there was less symptomatic improvement. This leads us to formulate the desirability of addressing these conflicts directly in psychotherapy as a way of enhancing its efficacy. To this end, our group has developed a manual of Dilemma Focused Therapy (DFT) published in English [41], Spanish [42] and Portuguese [43]. However, experience and data accumulated so far do not lead us to conceive DFT as enough for a comprehensive treatment for depression. The presence of dilemmas is not postulated as a causative agent nor as the only maintenance factor of depression (or of any other disorder) but rather as a cognitive structure that may hinder the process of change. For this reason, we do not conceive treatment of depression as using exclusively DFT, but rather propose DFT as an additional component to a broader treatment as a way to enhance efficacy.

### **Justification and main hypothesis**

The notion of mental or intrapsychic conflict has been discussed for over a century by multiple theoretical approaches, but it has not been defined in measurable operational terms. The importance of said conflicts with regard to depression has not been described either. Based on PCT, we have developed a procedure to identify IDs, a type of cognitive conflict, using RECORD 5.0 (44; the English version GRIDCOR 4.0 is also available in 27), an application software for the analysis of RGT data. Preliminary results [39] indicate that about 90% of these patients have at least one of the cognitive conflicts (dilemmas) as formulated by our team based on their repertory grids. These results justify the development of a manualized intervention, DFT, to resolve these conflicts [41-43].

The present study aims to adapt DFT to a specific individual intervention for unipolar depression combined with CBT in group format, the effectiveness of the latter having been demonstrated [e.g., 45]. In order to assess the efficacy of this combined package, it will be compared to patients receiving CBT both in group and individual format. If this new form of combined therapy (group CBT plus individual DFT) exceeds the efficacy of the condition that applies solely CBT (group plus individual) the project will have provided a potential improvement which, if applied, would produce significant benefits to depressive patients, and, consequently, for society in general. The reason for selecting CBT as the comparison group is the well-established level of efficacy of this therapy for depression, both in individual and group formats. Thus, this trial intends to test the hypothesis that the design of an intervention module focused on the dilemmas identified in each patient can contribute to improving the efficacy of cognitive therapy for depression.

### **Specific objectives**

- To study whether or not a combined therapy (group CBT plus individual DFT) is more efficacious than CBT applied in both group and individual formats.
- To check whether the degree of resolution of cognitive conflicts (dilemmas) is greater in the treatment condition specifically centered on dilemmas in comparison to the well-established CBT control treatment.
- To identify the pretreatment variables that predict the outcome of the two treatment conditions studied, in particular, diagnosis (Major Depressive Disorder, Dysthymic Disorder), chronicity, severity and cognitive indicators derived from the RGT.

### **Pilot studies**

Prior to the final version of this research protocol, two brief non-randomized studies were conducted consecutively to explore the best combination of group CBT and individual therapies (CBT and DFT) in terms of clinical applicability. Each study consisted of a small cohort of patients receiving a particular combination of these therapy formats. In the first study, after initial assessment (T1) two therapists conducted 10 group CBT sessions. Then, a new assessment (T2) took place before the next phase of individual therapy (10 sessions of CBT, or DFT for those patients with cognitive conflicts) carried out by different therapists. In the post-therapy assessment (T3) clients were interviewed in depth about the usefulness and convenience of the format of therapy received. They considered it helpful but mostly found the intermediate assessment in-between group and individual phases to be an interruption of the rhythm of treatment. In discussing the experience with therapists and supervisors it was also estimated that both phases could be shortened to 8 sessions without major loss. A second study was then conducted with another small cohort receiving a format of 8 group CBT sessions plus 8 individual (CBT or DFT) without the intermediate assessment. In this case, patients suggested that the continuity with the therapist from group to individual sessions would be more convenient. These pilot studies were useful not only for the better adjustment of the design with respect to the combination of the group and individual therapy formats, but also for the adaptation of the therapy manuals to be used in the main study.

## **Method**

### **Design**

This study follows a controlled trial methodology to evaluate the efficacy of treatments. Because DFT is not conceived as whole treatment for depression but rather as an ingredient which can be

added to other therapies, the study is designed to test the efficacy of a combined package including DFT as a substantial component. As a comparison group we use CBT for depression, a treatment package whose effectiveness is well established, both in individual and in group formats. Since DFT can only be applied in individual format (it focuses on the dilemmas identified specifically for each patient), group CBT is included as a shared part of both treatment conditions. This treatment modality has already been proven effective (to levels comparable to individual CBT format) and also more efficient in terms of treatment costs. In sum, all patients receive group CBT, and added to this condition is a component of individual therapy, which, depending on randomization can be CBT or DFT. For each treatment condition a therapy manual has been adapted for the specific format of the study. The design of the clinical trial is depicted in Figure 1.

**Figure 1 Clinical Study Design**

[figure not shown]

---

BDI-II, Beck Depression Inventory; CBT, Cognitive-behavioral therapy; CORE-OM, Clinical Outcomes in Routine Evaluation-Outcome Measure; HAMD, Hamilton Rating Scale for Depression; RGT, Repertory grid technique; SCID-I, Structured Clinical Interview for DSM-IV Axis I Disorders; SFB, Short Form B of the Clinical Outcomes in Routine Evaluation-Outcome Measure.

---

## Setting

The study will be conducted at various mental health centers in the Barcelona area: *CSM Nou Barris*, *Associació Catalana de Teràpies Cognitives (ACTC)* and others belonging to *Hospital de Mataró*, *Parc de Salut Mar* (Santa Coloma), and to *Fundació Sant Pere Claver*. Furthermore, patients will be recruited from primary care centers and treated either in those centers or at ACTC.

## Participants

Since this is the first controlled study of DFT, we don't have any previous data on which to base our estimations. But according to other studies comparing CBT with a variety of other therapies, we estimated medium between-group effects. Thus, to determine the sample size we calculated that with a statistical power of 0.80, considering a dropout rate of 20%, an  $\alpha$  significance level of 0.05 (two-sided) and an effect size of 0.30 we need a total of 112 patients. In terms of our primary outcome measure (BDI-II, see below) and based on Spanish normative data, calculation yielded a 3.3-point difference between groups.

*Inclusion Criteria:* All participants will meet diagnostic criteria for Major Depressive Disorder (MDD) or Dysthymic Disorder (DD) according to the DSM-IV-TR [46] and a score above 19 on the BDI-II questionnaire. Once the RGT is administered, only those patients who have at least one cognitive conflict are included in the treatment phase of the study, which based on previous data [39] it should be 90% of the cases. The age range is established between 18 and 70 years.

*Exclusion Criteria:* Patients presenting bipolar disorders, psychotic symptoms, substance abuse, organic brain dysfunction, acute suicidal ideation or mental retardation will be excluded from the study. Those who are receiving psychological treatment will not be accepted either, unless it is suspended at the time of inclusion in the study itself, in agreement with the patient and the therapist who is applying it. The presence of other comorbid conditions (anxiety, eating or personality disorders, etc.) and consumption of psychotropic drugs will not be cause for exclusion but they will be assessed and recorded for statistical control. Finally, those who do not have enough level of competence to communicate in Spanish or Catalan, or patients with substantial visual, hearing and cognitive deficits cannot be included.

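### The sample-size figures do not fit together: 112 patients follows from Cohen's f = 0.30 (d = 0.60), and the quoted 3.3 BDI-II points match that only if the SD is about 5.5

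*Protocol*

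**What the plan says.** The Participants section of the Protocol says that no earlier DFT data were available and that, from other comparisons of CBT with different therapies, "we estimated medium between-group effects". The calculation is then given as "with a statistical power of 0.80, considering a dropout rate of 20"%, two-sided alpha 0.05, and "an effect size of 0.30 we need a total of 112 patients". The next sentence moves to the primary outcome, the BDI-II: "based on Spanish normative data", the "calculation yielded a 3.3-point difference between groups".

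The section does not say whether 0.30 is a standardised mean difference (d), Cohen's f or something else. It gives no SD and names no test. It claims no gain from baseline adjustment or repeated measurement. The allocation ratio is not stated; I assume 1:1.

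**The concern.** A reader will take the paragraph to mean that 112 patients give 80% power to detect 3.3 BDI-II points. The most familiar reading of an effect size for a difference in means is d, and d = 0.30 needs about four times as many patients. The number of patients and the number of points appear to use the same 0.30 on two different scales.

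The interpretation of the trial depends on this. If the design is in fact sized for a difference larger than 3.3 points, a non-significant result could be reported as good evidence against a 3.3-point benefit of DFT when the trial had limited power to find one.

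**Working it through.** **Inputs from the Protocol (Participants).** Power 0.80; alpha 0.05 two-sided; dropout 20%; effect size 0.30, metric unnamed; total 112; BDI-II difference 3.3 points. **Assumed:** two equal arms, unadjusted two-sample t-test unless stated otherwise.

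**1. Reproducing 112.** Evaluable patients: 112 × 0.80 = 89.6, about 90, or 45 per arm.

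- 0.30 as Cohen's f, two groups: total N = 89.2; 89.2 / 0.80 = 111.5, rounded up to 112. This reproduces the figure.
- With two equal groups d = 2f, so f = 0.30 is d = 0.60. The t-test then needs 44.6, so 45 per arm; 90 / 0.80 = 112.5. This agrees within rounding.
- 0.30 as d: the normal approximation is n per arm = 2 × (1.960 + 0.842)² / 0.30² ≈ 174.4; the exact t calculation gives 175.4, so 176. Total 352 analysed; 352 / 0.80 = 440 enrolled.

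**2. Power with 45 per arm.** At d = 0.60: 80%. At d = 0.30: 29% (35% if all 112 are analysed, 56 per arm).

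**3. The BDI-II difference.** The points equal d × SD.

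- If d = 0.60, 3.3 points needs SD = 3.3 / 0.60 = 5.5.
- If 3.3 was obtained as 0.30 × SD, then SD = 3.3 / 0.30 = 11.0. At that SD, d = 0.60 is 0.60 × 11 = 6.6 points.

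**4. Power for 3.3 points by assumed SD** (90 analysed, unadjusted):

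| SD | d = 3.3 / SD | Power | Points at d = 0.60 |
|---|---|---|---|
| 5.5 | 0.60 | 80% | 3.3 |
| 7 | 0.47 | 60% | 4.2 |
| 8 | 0.41 | 49% | 4.8 |
| 10 | 0.33 | 34% | 6.0 |
| 11 | 0.30 | 29% | 6.6 |
| 12 | 0.275 | 25% | 7.2 |

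**5. Could the planned model close the gap?** The Statistical analyses section plans repeated-measures models with baseline as covariate, and there are three post-treatment assessments (T2, T3, T4). Take d = 0.30 and 90 analysed.

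- One visit, baseline-adjusted: effective d = 0.30 / √(1 − r²). At r = 0.5: 0.30 / 0.866 = 0.346, power 37%. At r = 0.7: 0.30 / 0.714 = 0.420, power 50%.
- Mean of three visits, baseline-adjusted, common correlation r, same effect at each visit: residual variance fraction v = (1 + 2r) / 3 − r², effective d = 0.30 / √v. At r = 0.3: v = 0.443, power 56%. At r = 0.5: v = 0.417, power 59%. At r = 0.7: v = 0.310, power 71%.

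All remain below 80%.

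**The case against.** The strongest reply is that the number of patients is correct. The Protocol never calls 0.30 a standardised mean difference, it plans analysis of variance, where f is a common metric, and it expects medium effects, which fits f = 0.30 better than d = 0.30. This stands. A reader might infer that 112 is a miscalculation and that 440 patients are needed. The document does not support that, because 440 applies only if 0.30 is d. What the reply does not rescue is the 3.3 points, which then require an SD near 5.5 that the Protocol neither states nor supports.

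A reader might also quote 29% as the trial's power for 3.3 points, or say that such a benefit would be missed about seven times in ten. Neither can be stated flatly. The 29% rests on an SD of 11 that is only inferred, and on an unadjusted comparison. The planned model could do better: 56% to 71% with three averaged visits and 90 analysed, and 81% if all 112 were analysed and the common correlation were 0.7. But the sample-size text does not invoke that gain, and it budgets for 20% dropout.

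Other origins of 112 are possible. A chi-square effect w = 0.30 needs 87.2 evaluable, about 109 to 110 enrolled, and 14 groups of 8 make 112. Cohen's f fits better, and w would not explain a difference in mean points. That one figure was used on two scales is therefore the likeliest explanation, not an established one.

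The Background remark that psychological treatments exist "without any single one of them standing out as more efficacious" might be read as showing that d = 0.60 is implausible. It is a general statement, and the comparative studies behind the expected effect are not in the document, so I do not rely on it.

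Finally, the Protocol already plans to consider confidence intervals and effect sizes, and its Discussion warns that a result without superiority would not rule out that DFT works. That warning concerns the combined-package design, not power for a stated difference.

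**Conclusion.** The paragraph is wrong as written. The effect size, the sample size and the BDI-II difference cannot all belong to one calculation unless the SD is about 5.5. On the reading that reproduces 112, the trial has 80% power for d = 0.60, and the detectable difference is 0.60 × SD: 3.3 points at SD 5.5, 4.8 at SD 8, 6.6 at SD 11. Unadjusted power for 3.3 points runs from 80% down to 25% as the SD goes from 5.5 to 12.

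This rests on 1:1 allocation, 90 analysed patients and, for the range, on assumed SDs. It does not show that more patients are needed. It shows that the claim of 80% power for 3.3 points is unsupported.

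**What to change.** Keep the sample size and rewrite the paragraph so that it:

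1. names the effect-size metric, the test, and the SD with its source, and justifies that SD for patients who score above 19 on the BDI-II (the Spanish BDI-II reference is titled as a general-population study);
2. states, if f is confirmed as the metric, that 112 enrolled (about 90 analysed, 45 per arm) give 80% power at two-sided 0.05 for f = 0.30, that is d = 0.60;
3. replaces 3.3 points with 0.60 × the justified SD (for example 6.6 points if that SD is 11; SD 11 should not be written in merely because it can be inferred);
4. gives the power actually available for 3.3 points under that SD, and, if credit is taken for baseline adjustment or repeated visits, the correlations assumed;
5. says that a non-significant result does not exclude a 3.3-point difference and that interpretation will rest on the confidence interval.

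The cost is one rewritten paragraph and a less favourable stated detectable difference. No patients are added.
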